#### Outcome analysis and reporting

The primary outcome variable, SPID, will be calculated using the pain-intensity difference (PID) at each time point outlined in Fig. 1, which is the difference between the patient’s pain level at that time on a standard 0–10 scale and the patient’s baseline pain level [25]. The SPID will be calculated by summing the pain intensity difference (PID) at each of the study time points, weighted by the amount of time since the prior assessment; this approximates the area under the curve for PID over time. SPID will also be reported as a percentage of maximum possible SPID.

Baseline patient characteristics and outcome measures will be reported using means and standard deviations, medians and ranges, or proportions as appropriate. Analysis of variance (ANOVA) and Student’s *t* test will be employed to determine differences between study arms for continuous measures, including the primary outcome of SPID, and the Fisher’s exact test will be used for differences in categorical variables. Two-way ANOVA testing with repeated measures in one factor (time) will be performed to compare the effect of treatment arm over time on pain-intensity measures.

Missing data will be handled using multiple-imputation models and standard error uncertainty estimates in which missing data will be replaced using summary outcomes from participants with complete data for each variable of interest. To assess the robustness of the models, sensitivity analyses will be performed in which the primary outcome will be compared with and without those lost to follow-up included and assumed to have the mean SPID correlating to the allocation arm of initial randomization.

Prior to trial initiation, a statistical analysis plan with formalized procedural protocols will be created. Analyses will be performed using STATA 13.0 (StataCorp LP, College Station, TX, USA). A *p* value of less than 0.05 will be considered significant for all analyses. All data analyses will be coded on program files to allow independent reproduction of analyses.

Reporting of outcomes will follow the most up-to-date Consolidated Standards of Reporting Trials (CONSORT) guidelines as well as the extensions to equivalence trials; and to nonpharmacological interventions. The collected data set will also be made available in conjunction with the associated trial report.

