## Methods

### Design

The RAPID study will be conducted in the aftermath of a major earthquake to which a Médecins Sans Frontières (MSF) field hospital is deployed at the request of the local Ministry of Health (MoH). The study design is a blinded RCT using an equivalence design. After obtaining informed consent, earthquake victims with serious lower extremity injuries will be randomized to one of three study arms. Eligible participants will be randomized in a 1:1:1 allocation ratio to either: standard care (defined below); standard care plus an anatomic landmark-guided FICB; or standard care plus an US-guided FNB. The structure of the study is illustrated in Fig. 1.

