### Outcome measures

The primary outcome measure will be the summed pain intensity difference (SPID), a commonly used measure to assess efficacy of various pain management interventions [25, 32]. While the SPID has not been previously validated in a post-earthquake setting, it has been used in a variety of clinical settings around the world. SPID measures pain over time and controls for both cultural and individual differences in pain perception and expression. To calculate the SPID, participants will be asked to estimate their pain using a standard 11-point Numerical Rating Scale (NRS) at baseline (prior to treatment) and at set time points over the subsequent 24 h of follow-up (Fig. 3). The SPID will be calculated as the area under the curve describing the difference between current and baseline pain intensity at each time point.

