#### Inclusion/exclusion criteria

The RAPID study will include adult patients (18 years or older) presenting to the MSF field hospital with one or more lower limb injuries. The trial will exclude patients with multisystem trauma, severe respiratory distress, hypotension, altered mental status, active infection at the sight of injection, known current pregnancy, and those who are unable to provide informed consent. Patients with known allergies to local anesthetic agents or narcotic pain medication, those receiving antithrombotic therapy or with a preexisting coagulopathy, and those likely to receive regional anesthesia for alternative reasons within 2 h of screening will also be excluded.

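### The primary SPID comparison does not adjust for baseline pain: it is valid, but it gives up precision that the already collected baseline NRS would supply at no cost

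*Protocol article*

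**What the plan says.** Under Outcome analysis and reporting, the article names ANOVA and Student's t test, which "will be employed to determine differences between study arms for continuous measures, including the primary outcome of SPID". No covariate is mentioned. The over-time analysis, a two-way repeated-measures ANOVA, has only arm and time as factors.

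Baseline enters through the definition of the outcome. The pain-intensity difference is defined by the clause "which is the difference between the patient’s pain level at that time on a standard 0–10 scale and the patient’s baseline pain level". SPID sums these differences, "weighted by the amount of time since the prior assessment; this approximates the area under the curve for PID over time". One baseline-scaled version is promised as an additional report: "SPID will also be reported as a percentage of maximum possible SPID".

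Outcome measures gives a rationale for the choice: "SPID measures pain over time and controls for both cultural and individual differences in pain perception and expression". The same section says that pain is scored "at baseline (prior to treatment) and at set time points over the subsequent 24 h of follow-up", so baseline NRS is available for every participant.

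Randomization and blinding describes 1:1:1 allocation in blocks of six and states no stratification by pain. On who enters, Design says that "earthquake victims with serious lower extremity injuries will be randomized to one of three study arms", while the criteria read: "The RAPID study will include adult patients (18 years or older) presenting to the MSF field hospital with one or more lower limb injuries".

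**The concern.** A change score is often taken to have dealt with baseline because baseline has been subtracted. It has not. A patient with little pain at entry has little room to improve and a patient with severe pain has much, so SPID will generally still vary with baseline within each arm. The Outcome measures rationale suggests that the issue is closed, and the named test then leaves that source of variation in the error term.

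Two things are at stake. The confidence interval used to judge equivalence is wider than it need be. And if the arms happen to differ in baseline pain, the unadjusted difference carries part of that imbalance, with nothing in the primary analysis to take it out. The trial gets one recruitment opportunity, after an event nobody can schedule, so precision from data already collected is worth having.

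The entry criteria bear on this indirectly. They set no pain or severity requirement, and the word serious in Design is not defined. The text therefore does not limit how far baseline scores may spread.

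**Working it through.** **Inputs from Sample size:** SD up to 20, true difference 0, equivalence margin 13, one-sided 2.5 %, 63 per arm before attrition, 90 % power.

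**Inputs not in the document:** r, the within-arm correlation of baseline NRS with SPID (shown as a range), and the time unit of the SPID weights (hours assumed). Relief is counted as positive.

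**1. The plan's own figure.** For two one-sided tests with a true difference of 0:

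n = 2 × [SD × (z0.975 + z0.95) / margin]² = 2 × [20 × (1.960 + 1.645) / 13]² = 61.5, so 62 per arm.

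With the noncentral t distribution, power is 89.7 % at 62 and 90.3 % at 63. The stated 63 is reproduced, using the full SD of 20 with no reduction for baseline.

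**2. Dependence on baseline.** If pain falls to 0 at once and stays there, each hour contributes the baseline score, so the maximum SPID is 24 × baseline NRS: 72 at baseline 3, 192 at baseline 8, 216 at baseline 9. Subtraction leaves this ceiling in place.

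**3. Gain from adjustment.** With baseline NRS as a linear covariate, the residual SD is 20 × √(1 − r²), and the share of variance removed is r². The 95 % half-width is 1.96 × residual SD × √(2/63). Power is recomputed as in step 1. The degree of freedom spent on the slope is ignored, which is immaterial at this size.

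| r | Variance removed | Residual SD | 95 % CI half-width | Equivalence power, 63 per arm |
|---|---|---|---|---|
| 0 (unadjusted) | 0 % | 20.0 | 6.98 | 90.3 % |
| 0.2 | 4 % | 19.6 | 6.84 | 91.7 % |
| 0.3 | 9 % | 19.1 | 6.66 | 93.3 % |
| 0.5 | 25 % | 17.3 | 6.05 | 97.4 % |
| 0.7 | 49 % | 14.3 | 4.99 | 99.8 % |

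**4. Effect of a realised imbalance.** Let s be the baseline SD. The slope of SPID on baseline is r × 20 / s, and the standard error of the baseline difference between two arms is s × √(2/63). Their product does not involve s. An imbalance of one standard error therefore moves the unadjusted difference by r × 20 × √(2/63) = r × 3.56 units. For two standard errors:

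- r = 0.3: 2 × 0.3 × 3.56 = 2.1 units, 16 % of the margin
- r = 0.5: 2 × 0.5 × 3.56 = 3.6 units, 27 %
- r = 0.7: 2 × 0.7 × 3.56 = 5.0 units, 38 %

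**5. What r might be.** This is illustration only, on assumptions outside the document: relief proportional to baseline, mean SPID 65 (from 13 / 0.20, reading the margin as the stated 20 % change), baseline mean 6 to 8, baseline SD 1 to 2.5, and SD of the relief fraction 0.1 to 0.3. Simulated r ran from about 0.14 to 0.86. In the scenarios whose SPID SD was near the stated 20 (18 to 23), it was about 0.4 to 0.7.

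**The case against.** The strongest reply is that nothing here is invalid. Over repeated randomisations the unadjusted t test is unbiased with correct type I error, chance imbalance is already part of its standard error, and the sample size is right on its own inputs. All of that stands. What remains is efficiency, plus error conditional on the imbalance that actually occurs.

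Second, baseline is not ignored: it is subtracted in every pain difference, and the percentage of maximum SPID rescales for the ceiling in step 2. This is a partial answer, because that version is an additional report and not the named primary comparison.

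Third, covariates are commonly settled in the statistical analysis plan, which the article promises before the trial starts and which is not shown here. It may add the covariate. But the article does more than stay silent: it names an unadjusted method for the primary outcome.

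Fourth, the Outcome measures sentence concerns perception and expression of pain, and subtraction does remove a constant personal offset in how the scale is used. The sentence is too strong, but not baseless.

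Fifth, the baseline spread may be modest. Data collection expects participants to have substantial physical trauma, and no baseline distribution is given. That is why r is shown as a range.

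A reader might infer a larger effect. With baseline SD 2, equal post-dose SD and a correlation of 0.5 between them, a half-point imbalance has probability 0.16 (standard error 2 × √(2/63) = 0.356) and moves SPID by 0.5 × (1 − 0.5) × 24 = 6 units, nearly half the margin. But those assumptions give a change variance of 2 × (1 − 0.5) × 4 = 4, hence a SPID SD of 2 × 24 = 48. The margin of 13 is paired in the protocol with an SD of 20. Holding SD 20 in the same model, the baseline SD is 20 / 24 = 0.83 and a half-point imbalance has probability about 0.0008. An imbalance with probability 0.16 (1.4 standard errors) then moves the difference by 1.4 × 0.5 × 3.56 = 2.5 units, 19 % of the margin.

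Likewise, a power gain from about 95 % to 99 % at r = 0.5 refers to detecting a difference of 13. The protocol states power for showing equivalence, so the table in the working applies.

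**Conclusion.** The point holds as a free improvement, not as an error of validity. The article fixes an unadjusted primary comparison of an outcome whose range depends on a baseline measured in everyone. The gain from adjusting is slight at r = 0.2 and material from about r = 0.5 upward. The direction is secure; the size is not, because the document gives no r.

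The figures assume the protocol's SD of 20, margin of 13 and 63 evaluable patients per arm, a linear relation of SPID to baseline with a common slope across arms, and, for the ceiling only, hourly weights.

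The documents do not support saying that the planned test is biased, that the sample size is wrong, or that a likely imbalance would move the estimate by an amount comparable to the margin. Nor do they show that many patients will enter with little pain. They show only that Design and the inclusion criteria describe the population differently.

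**What to change.** - Make the primary comparison a linear model (ANCOVA) of SPID on arm with baseline NRS as covariate, and take the equivalence confidence interval from that model. Keep the unadjusted t test as a sensitivity analysis.
- Use the same covariate in the over-time model.
- Soften the Outcome measures statement: SPID removes a constant personal offset in scale use, but does not make the result independent of baseline pain.
- Separately, the investigators should reconcile the serious injuries of the Abstract and Design with the broader wording of the inclusion criteria. No entry threshold is proposed here.

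The analysis change needs no new data and no more patients, since baseline NRS is already recorded. According to Trial status, the study had yet to commence, so the change can be written into the analysis plan before any outcome exists. The sample size can stay at 63 per arm before attrition, with the gain taken as extra power.

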### Randomization and blinding

Randomization will occur immediately following informed consent attainment. Study subjects will be individually allocated in a 1:1:1 parallel format into three distinct study arms via blocked randomization with six subjects per block. Allocation will be achieved using sealed envelopes containing computer-generated and preprinted randomization assignments with unique patient identification numbers.

The enrolled participants and the treating health care teams will be blinded to the patient’s allocation arm through uniform exposure to US scanning and injection procedures as outlined below. Only the research team proceduralist delivering the injection will know the intervention received by the patient.

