### Research personnel training and deployment

Prior to initiation of the trial, and preceding the earthquake event, a cohort of MSF nurses and physicians will be trained in study procedures via a structured interactive course. These practitioners will make up the international portion of the RAPID research team, responsible for data collection and procedural activities. The training will cover all study procedures, including both anatomic landmark- and US-guided femoral nerve blockade for RA [18, 36]. For each trainee, minimum competence will be assessed using a didactic knowledge test and assessment of procedural abilities through direct observation using phantom training models. All research team members will participate in an additional and mandatory Good Clinical Practice (GCP) training.

Within 72–96 h of the earthquake event, members of the RAPID research team will be deployed alongside the MSF response team and field hospital to the site of the disaster. The research team will be divided into shifts, to facilitate 24-h enrollment; each shift will include, at minimum, one data collector, a proceduralist, and a local translator.

As outlined in Fig. 2, study coordinators will also hold an onsite procedural training for locally recruited health care providers, who will take over as the RAPID proceduralists during the latter half of the study. These providers will be trained and assessed onsite using the same methods as the international portion of the research team.

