### Statistical analysis

#### Sample size

The sample size for this study uses a framework of an equivalency trial with parenteral morphine as the standard of care versus morphine with RA as the novel treatment. The new modality is further divided into two arms of RA: FICB and US-guided FNB. For the purpose of this study, a clinically important effect size was defined as a 20 % change in the primary outcome of the SPID. Based on this assumption, a sample size of 63 patients per arm provides 90 % power to show equivalence between each group (e.g. RA administered via FICB as compared to standard care or RA performed using a FNB versus standard care), assuming a standard deviation (SD) up to 20, a difference between the SPID group means of 0 and an equivalence of 13, at a 2.5 % significance level (one-sided). Allowing for 10 % attrition, the sample size is 69 patients per arm, with 207 participants in total.

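### SPID is compared with unadjusted ANOVA and t tests although blocking balances the arms over enrolment and proceduralists change mid-study; one prespecified period term could recover a little precision if SPID drifts

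*Protocol article*

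**What the plan says.** Three parts of the protocol article bear on this.

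- **Outcome analysis and reporting** names ANOVA and Student's t test, which "will be employed to determine differences between study arms for continuous measures, including the primary outcome of SPID". No term for block, enrolment period or proceduralist group is mentioned. The two-way repeated-measures ANOVA in the same section uses time within the 24-h follow-up, which is a different time axis from date of enrolment.
- **Randomization and blinding** allocates patients 1:1:1 "via blocked randomization with six subjects per block". No stratification factor is stated.
- **Research personnel training and deployment** plans for locally recruited providers "who will take over as the RAPID proceduralists during the latter half of the study". It adds: "These providers will be trained and assessed onsite using the same methods as the international portion of the research team".

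The **Sample size** section plans for equivalence, "assuming a standard deviation (SD) up to 20", with "a difference between the SPID group means of 0 and an equivalence of 13". It arrives at 63 patients per arm for 90 % power at one-sided 2.5 %, and 69 per arm (207 in total) after attrition. A statistical analysis plan is announced but is not among the documents shown.

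**The concern.** With two patients per arm in every complete block of six, the arms are almost exactly balanced at each stage of enrolment. A change in SPID level that affects all arms alike therefore cancels from the arm difference. An unadjusted t test or ANOVA does not use this: its pooled variance is taken around arm means for the whole trial, so any difference between early and late patients counts as noise.

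The design builds in one known change over enrolment, the handover of proceduralists. The case mix may change as well as the days pass after the earthquake, but that is inference; the article does not say so.

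What is at stake is precision on the primary outcome: confidence intervals for SPID slightly wider than the design allows, whether the final claim is equivalence or a difference.

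**Working it through.** **Inputs.** From Sample size: SD 20, margin 13, true difference 0, one-sided 2.5 %, 63 per arm. From Randomization and blinding: blocks of six over three arms. The size of any drift is not in the documents. I assume a step of D SPID units between two equal halves and vary D.

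**1. The plan's own figure.** For two one-sided tests at true difference 0:

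n = 2 × [20 × (1.960 + 1.645) / 13]² = 61.5, so 62 per arm.

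With the t distribution, power is 89.7 % at 62 and 90.3 % at 63. The stated 63 reproduces, as an unadjusted comparison with overall SD 20. The unadjusted standard error is 20 × √(2/63) = 3.563.

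**2. Shift common to all arms, total SD held at 20.** The period share of variance is r = (D/2)² / 400. The adjusted SE is 3.563 × √(1 − r), so the unadjusted SE is too large by 1/√(1 − r) − 1.

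| D (SPID units) | r | Adjusted SE | Excess of unadjusted SE |
|---|---|---|---|
| 0 | 0 | 3.563 | 0 % |
| 5 | 1.6 % | 3.536 | 0.8 % |
| 8.9 | 5.0 % | 3.474 | 2.6 % |
| 10 | 6.3 % | 3.450 | 3.3 % |
| 13 (the margin) | 10.6 % | 3.370 | 5.7 % |
| 20 (one SD) | 25 % | 3.086 | 15.5 % |

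If SD 20 is read as the within-period SD, the excess is √(1 + D²/1600) − 1: 0.8 %, 3.1 % and 5.1 % for D = 5, 10 and 13. A split other than half and half makes r smaller.

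**3. Simulation of step 2.** 204 patients in 34 blocks of six, total SD 20, no arm effect, 8,000 runs per row, two-sided 5 % tests. The Monte Carlo error of a rejection rate is about √(0.05 × 0.95 / 8000) = 0.24 points.

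| D | True sampling SD | Unadjusted SE | SE with period term | Type I error, unadjusted | Type I error, with period |
|---|---|---|---|---|---|
| 0 | 3.44 | 3.42 | 3.42 | 5.1 % | 5.1 % |
| 5 | 3.45 | 3.43 | 3.40 | 5.1 % | 5.3 % |
| 10 | 3.28 | 3.43 | 3.31 | 4.1 % | 4.8 % |
| 20 | 2.97 | 3.43 | 2.97 | 2.4 % | 4.9 % |

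**4. Equivalence power.** Simulated with 64 per arm, margin 13, true difference 0 and a common mid-study step. Power without and with adjustment was 91.0 % and 90.8 % with no step, 91.3 % and 92.4 % at D = 8.9, and 92.0 % and 93.8 % at D = 12.6. The adjusted figures used block terms; a single period term performed the same.

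**5. Shift only in the two nerve-block arms.** Take within-period SD 20. In a comparison of control with one block arm, the unadjusted variance is 400 + D²/8, and with a period main effect it is 400 + D²/16. The SE excess over the adjusted SE is then:

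- D = 5: √(403.1/401.6) − 1 = 0.2 %
- D = 10: √(412.5/406.3) − 1 = 0.8 %
- D = 13: √(421.1/410.6) − 1 = 1.3 %

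If the variance is pooled over all three arms, the two variances are 400 + D²/6 and 400 + D²/18, and the excess is 0.3 %, 1.4 % and 2.3 %. A simulation with 204 patients agreed with both sets to within 0.1 point. The remaining D²/16 or D²/18 is the arm-by-period interaction, which the main-effect term leaves in the error.

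**6. Block terms or one indicator?** For a step, the two give the same SE. For a linear drift of 20 units over the whole enrolment, the simulated SE was 3.43 unadjusted, 3.32 with the period indicator and 3.28 with block terms. One indicator recovers most of what 34 block terms would.

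**The case against.** The strongest reply is that nothing here is an error. A permuted block is an allocation device and not a stratification factor. The t test is unbiased and its type I error is at or below nominal. The sample size assumes the same unadjusted comparison, so the promised power is delivered. Model covariates are commonly left to the analysis plan, which the article announces. All of this stands, and it fixes the level of the point: a small improvement, not a defect or a contradiction. What remains is that the article does not leave the primary test open. It names an unadjusted one, beside a design that balances the arms over a planned handover.

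Second, the gain depends on a drift that nobody has measured. The documents give no such figure, and both groups of proceduralists are trained and assessed by the same methods. A common shift as large as the margin would be a big effect. This stands too.

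Third, the handover is the only documented change, and in the control arm the injection is subcutaneous saline. Proceduralist skill should therefore act mainly in the two nerve-block arms, where a period main effect recovers little (step 5). This is right. The larger figures apply only to a drift shared by all arms.

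**Conclusion.** The point holds as a minor, conditional gain in precision. If SPID shifts between the two halves in all arms, the unadjusted SE exceeds the adjusted one by under 1 % at 5 units, about 3 % at 9 to 10 units and about 5 % near 13 units. With no shift the excess is nil. If the shift is confined to the two nerve-block arms, the excess for control against one block arm is about 1 % or less up to 10 units. These figures rest on SD 20, equal halves and a step change. The size of D is an assumption throughout.

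A reader might infer more, and the documents do not support it:

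- **That the standard error is too large as a matter of fact.** It is correct if there is no drift, and no drift is quantified.
- **That the trial is biased or underpowered.** Blocking protects the contrast, the error rate falls rather than rises, and 63 per arm reaches 90.3 % with the unadjusted test.
- **That all the blocks must be in the model.** One period indicator does nearly as well.

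**What to change.** In Outcome analysis and reporting, or in the analysis plan before the trial starts, replace the unadjusted primary comparison with a linear model for SPID containing arm and one enrolment-period indicator (before or after the proceduralist handover). Read the arm contrasts and their 95 % confidence intervals from that model. Define the indicator by the handover itself, so that its boundary cannot be chosen from the outcome data. About 34 block terms are not needed.

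The cost is one sentence and one residual degree of freedom, and with no drift the simulated SE and error rate are unchanged. The trial has not begun and the analysis plan is still to be written, so the term can be fixed before any data exist. Added later, it would be open to challenge.

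The main-effect term does not address an arm-by-period interaction, that is, a block effect that differs between international and local proceduralists. If that question matters, it needs its own prespecified secondary analysis.

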### Data collection

Data collection time points are outlined in Fig. 1. Study personnel will assess the subject’s pain score and vital signs at baseline and again at eight predetermined intervals using the 11-point NRS (Fig. 3). Adverse events will be monitored throughout the follow-up period. Additionally, subject satisfaction with their care and total amount of required analgesic medications will be assessed at the conclusion of the study for each participant. Baseline demographic characteristics and information on mechanism of injuries will also be gathered at the time of enrollment. As the population being evaluated will be followed-up for only 24 h at a single study site and will have substantial physical trauma, it is likely that losses to follow-up through discharge prior to 24 h or patients leaving against medical advice will be minimal.

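### The repeated-measures ANOVA named for pain over time is too liberal for its time and arm-by-time tests if sphericity fails and no correction is applied; a mixed model with unstructured covariance would serve better

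*Protocol article*

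**What the plan says.** In the protocol article, Outcome analysis and reporting names the method for the course of pain: "Two-way ANOVA testing with repeated measures in one factor (time) will be performed to compare the effect of treatment arm over time" on pain-intensity measures. It sets one significance threshold, 0.05, for all analyses. Pain is scored "at baseline and again at eight predetermined intervals using the 11-point NRS" (Data collection), so there are nine scores per patient, the later ones "at set time points over the subsequent 24 h of follow-up" (Outcome measures). Each SPID term is "weighted by the amount of time since the prior assessment", which allows for unequal spacing. The actual times are in Fig. 1, which is not shown.

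This is a supporting analysis. The primary outcome is one SPID value per patient, for which ANOVA and the t test "will be employed to determine differences between study arms for continuous measures, including the primary outcome of SPID". Pain by time point is not among the listed secondary outcomes. The same section plans multiple imputation for missing data and announces a separate statistical analysis plan, which is not shown.

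**The concern.** The classical univariate tests of time and of arm by time require sphericity: the differences between every pair of times must have the same variance. Equal variances with equal correlations are sufficient for this, though not necessary. Pain scores over 24 h could easily depart from it. A block wears off, further analgesia is given at the treating team's discretion, and neighbouring scores resemble each other more than distant ones. If the times cluster early, the departure grows.

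When sphericity fails, the F statistic behaves as if it had fewer degrees of freedom than the table assigns, and the uncorrected p value is too small. The consequence here would be a false report that the arms differ in their course of pain. Even a valid joint F test would not say at which times the arms differ, and that is the useful clinical reading of such data.

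**Working it through.** **Inputs from the protocol article.** Three arms, allocated 1:1:1; 63 evaluable patients per arm (Sample size); baseline plus eight scores (Data collection); significance at 0.05 (Outcome analysis and reporting).

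**The plan's own figure.** The article gives no figure for the repeated-measures analysis. The one figure used here is 63 per arm. Two one-sided tests with SD 20, margin 13, true difference 0, one-sided 2.5 % and 90 % power give n = 2 × [20 × (1.960 + 1.645) / 13]² = 61.5, so 62. Power at 63 is 2Φ(13 / (20√(2/63)) − 1.960) − 1 = 90.9 %. The stated figures are reproduced closely enough, and 63 per arm is used below.

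**Degrees of freedom.** With k = 3 arms, N = 189 patients and T = 8 times, the arm-by-time test has (k − 1)(T − 1) = 2 × 7 = 14 and (N − k)(T − 1) = 186 × 7 = 1302 degrees of freedom. Its uncorrected 5 % critical value is 1.70.

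**Departure from sphericity.** ε = [tr(A)]² / [(T − 1) tr(A²)], where A is the covariance matrix of the scores centred within patient. ε = 1 means sphericity holds. The F statistic then follows approximately an F distribution with ε × 14 and ε × 1302 degrees of freedom.

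**Assumptions, because Fig. 1 is not shown.** Even schedule: every 3 h to 24 h. Front-loaded schedule: 0.25, 0.5, 1, 2, 4, 8, 12 and 24 h. Correlation at lag d hours: equal (0.5); mild decay (0.3 + 0.5 × 0.8^d for d > 0); strong decay (0.9^d). Each setting has 4000 simulated trials with no arm effect. The Monte Carlo standard error at 5 % is √(0.05 × 0.95 / 4000) = 0.34 percentage points.

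Rejection rate of the arm-by-time test at nominal 5 %, eight post-baseline scores:

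| Schedule | Correlation | ε | Uncorrected, simulated | Uncorrected, F approximation | Greenhouse-Geisser | Unstructured (Wilks) |
|---|---|---|---|---|---|---|
| Even | equal | 1.00 | 5.2 % | 5.0 % | 4.8 % | 4.9 % |
| Even | mild decay | 0.85 | 6.9 % | 6.2 % | 5.8 % | 5.0 % |
| Even | strong decay | 0.53 | 9.6 % | 10.2 % | 4.6 % | 5.1 % |
| Front-loaded | equal | 1.00 | 4.7 % | 5.0 % | 4.5 % | 4.8 % |
| Front-loaded | mild decay | 0.75 | 6.9 % | 7.2 % | 4.6 % | 4.5 % |
| Front-loaded | strong decay | 0.44 | 10.4 % | 11.7 % | 4.3 % | 4.7 % |

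Worked row (front-loaded, strong decay): 0.44 × 14 = 6.2 and 0.44 × 1302 = 573 degrees of freedom. The correct critical value is about 2.10, not 1.70, and an F distribution with the reduced degrees of freedom exceeds 1.70 with probability about 11.7 %.

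**With baseline as a ninth score.** Uncorrected: 5.0 to 5.2 % under equal correlation, 6.8 to 7.1 % under mild decay, 10.8 to 11.5 % under strong decay. A separate set of runs, with three assumed schedules, a shared correlation component of 0.3 and decay over 3 or 8 h, gave 6.5 to 12.4 % for ε from 0.81 to 0.40.

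**What is not affected.** The test of the arm average over time stayed at 4.4 to 5.7 % in all twelve settings of the first set of runs. SPID is one value per patient, so sphericity does not enter its comparison or the sample size.

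**Limit of the check.** The unstructured column is a multivariate test on complete data. It stands in for the proposed mixed model and leaves out the baseline covariate.

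**The case against.** The strongest reply is that repeated-measures ANOVA is a sound method once corrected, that nothing says the uncorrected p value will be used, and that the correction is ordinary content for the announced statistical analysis plan. Much of this stands. The absence of a correction from the article is not in itself an error, and Greenhouse-Geisser held the error rate at 4.3 to 5.8 % in all twelve settings. What remains is that the article fixes a method, and a better one is available on the same data at almost no cost.

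It is also fair to say that a mixed model is not better by name alone. With only a random intercept it implies equal correlation, and on balanced data it returns the same F test. The gain depends on the covariance structure.

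Three stronger readings are tempting, and the documents do not support them:

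- A reader might infer that the p values will be too small. That requires sphericity to fail and no correction to be used, and it applies only to tests involving time.
- A reader might infer that patients with an incomplete set of scores would be dropped, with loss of power or bias. The article plans multiple imputation and expects minimal loss to follow-up over 24 h at a single site.
- A reader might infer that the trial's main conclusion is at risk. The primary analysis does not use this test.

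**Conclusion.** The point holds as a modest improvement to a supporting analysis. If sphericity fails and the uncorrected p value is read, the arm-by-time test rejects about 7 to 12 % of the time at a nominal 5 %. The lower end is a slight excess, and the upper end needs the strongest departures assumed (ε about 0.4). Under equal correlation there is no excess. These sizes rest on assumed assessment times and correlations, so they show what could happen and do not estimate this trial's error rate.

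**What to change.** Replace the sentence on two-way repeated-measures ANOVA with a linear mixed model for repeated measures. The outcome is the NRS score at the eight post-baseline times. The fixed effects are arm, time as a categorical factor, arm by time, and baseline NRS. The within-patient covariance is unstructured. Report the arm contrasts with 95 % confidence intervals at each time; intervals also suit a trial described as an equivalence design.

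If the ANOVA is kept, state that the Greenhouse-Geisser p value decides for time and arm by time.

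The cost is a change of wording in the protocol and the statistical analysis plan, with no new data and no change in sample size. The named software can fit the model. An unstructured covariance for eight times has 8 × 9 / 2 = 36 parameters, to be estimated from about 189 patients (3 × 63).
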